### Harms

All AEs occurring in the 7 days following booster vaccinations will be recorded on the electronic case report form (eCRF). Events will be MedDRA coded at data entry and details of their duration, severity, relatedness to the vaccination and management will be collected. All AEs and serious adverse events (SAEs) not related to participants’ underlying medical condition that qualified them for the trial, or to its treatment will be recorded on the eCRF. SAEs will be monitored continuously throughout the trial and will be recorded on both the eCRF and separately for onward reporting to the sponsor and ethics committee within 24 hours of an investigator becoming aware.

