### Outcomes

The primary outcome will be the integrated time-weighted area under the curve (AUC) anti-SARS-CoV-2 NAb response over 12 months from a SARS-CoV-2 booster as assessed by a high-throughput SARS-CoV-2 NAb platform assay developed by our group.^22^,^24^ The assay involves culturing a cell-line that is hyper-permissible to SARS-CoV-2 through the expression of ACE2 and transmembrane serine protease 2 receptors. Serial dilutions of patient serum are then introduced to the cell culture wells in addition to homogenous concentrations of SARS-CoV-2 virions including variants of concern. Anti-spike IgG present in the patient serum acts to block viral entry into the cell. The assay readout is the infectious dose 50% (ID_50_), the viral concentration required to obtain 50% cellular death.

Secondary outcomes include laboratory, safety and clinical/biological outcomes:

Laboratory outcomes:

NAb response to a tetanus toxoid booster integrated over 12 months.Responses to the COVID-19 vaccine includingBreadth of NAb against SARS-CoV-2 variants of concern.Kinetics of NAb over time including responses to variants of concern.Memory T cell, B cell and natural killer (NK) cell responses to peptide sets representing different domains of the SARS-CoV-2 spike protein.Immunological responses as assessed above in populations stratified by broad study-qualifying disease type and different modes of immunosuppression employed such as chemotherapy, BMT, B-cell depleting therapies and cytokine inhibition.

Safety outcomes:

Local and systemic AEs that occur in the 7 days following the DT and COVID-19 vaccinations.AEs following immunisation and adverse drug reactions following immunisation for the duration of the study.COVID-19 vaccine-induced disease flares.On-study PCR-confirmed or rapid antigen-confirmed SARS-CoV-2 infections.All on-study pregnancies.

Clinical/biological outcomes:

Health quality of life scores (EQ-5D-3L) at weeks 0, 24 and 48.Impact of immunosuppression on vaccine protection over time will be assessed by modelling:Level of protection over time based on NAb levels.Boosting and decay of anti-spike IgG, specific memory B, T and NK cell responses.Inform policies on the timing of additional COVID-19 boosters in vulnerable populations about to commence immunosuppression or following BMT.

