#### Interim analyses

An interim safety analysis of full summary data examining booster vaccine-associated AEs, vaccine-induced disease flares and breakthrough COVID-19 infections will be performed when 30% (100) of participants reach the 24-week time point. A second safety analysis and an efficacy analysis examining the primary endpoint will be performed when 50% (160) of participants have reached 12 months. Additional meetings at which full interim data summaries will be reviewed may be scheduled following the occurrence of repeated or unresolved clinical events such that the Co-ordinating Principal Investigator (CPI) and DSMB Chair feel a full interim safety summary is warranted, or if the first DSMB meeting indicates a further meeting is warranted prior to all participants completing the study.

DSMB meeting reports will include open and closed session reports. Open session reports will include data on study conduct, protocol compliance, recruitment, baseline and follow-up characteristics and will be distributed to the PSC Chair, study statistician and DSMB members. Outcome results will not be discussed at open sessions. Closed session reports will be provided as unblinded reports and distributed only to DSMB members who will discuss outcome results, make decisions and formulate recommendations.

Following each DSMB review of full safety data, the DSMB will recommend to the PSC through the PI to (a) continue the study without modification, or (b) continue with stated modifications, or c) terminate the study.

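### After day 7, a non-serious disease flare is counted only if unblinded site staff attribute it to the vaccine, although flares are a safety outcome and a DSMB measure

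*Protocol article*

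**What the plan says.** The Harms section of the protocol article contains three recording statements.

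- Around each vaccination there is no filter on cause: "All AEs occurring in the 7 days following booster vaccinations will be recorded on the electronic case report form (eCRF". For these events, "details of their duration, severity, relatedness to the vaccination and management will be collected".
- For the rest of the study, the AEs and SAEs to be recorded are those "not related to participants’ underlying medical condition that qualified them for the trial, or to its treatment will be recorded on the eCRF".
- The next sentence is about serious events and does not repeat that exclusion: "SAEs will be monitored continuously throughout the trial and will be recorded on both the eCRF and separately for onward reporting".

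The safety list under Outcomes includes "COVID-19 vaccine-induced disease flares", with no time limit. It is a separate item from "AEs following immunisation and adverse drug reactions following immunisation for the duration of the study". The Interim analyses section gives flares to the DSMB as one of three safety measures: "An interim safety analysis of full summary data examining booster vaccine-associated AEs, vaccine-induced disease flares and breakthrough COVID-19 infections will be performed", timed for when 100 participants have reached week 24.

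The Blinding section explains that neither participants nor research staff could be blinded, because the two vaccines are given in different places. The Data collection methods section describes what is gathered at visits as clinical data, concomitant medication, AEs and SAEs. It names no flare item.

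**The concern.** A flare belongs to the class of event that the general rule leaves out: it is activity of the disease that qualified the participant. It enters the count only if someone first decides that the vaccine caused it. That decision is made by staff who know which booster was given and when. Relatedness is normally a field completed on a recorded event. Here it also decides whether the event is recorded at all.

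Two things are at stake. The DSMB may be shown a flare count whose numerator has been filtered by knowledge of the arm. The trial may also lose a comparison that its design offers. In Group 1, weeks 0 to 24 set a COVID-19 booster against a DT booster by randomisation, so counting all flares by arm would address causation without any individual attribution. Six of the seven Group 1 sub-strata (6 × 40 = 240 of 280 participants) have autoimmune or inflammatory disease, where a flare is an obvious safety question.

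**Working it through.** The plan gives no flare rate, so there is no figure of its own to reproduce. The check compares the sections and then works out how far the gap extends.

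**Step 1: which flares are recorded under the Harms section?**

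- Any flare within 7 days of a booster: recorded, whatever its cause.
- A non-serious flare after day 7, judged to be disease activity: related to the qualifying condition, so outside the rule.
- A non-serious flare after day 7, judged vaccine-induced: recorded, and counted under Outcomes.
- A serious flare after day 7, judged to be disease activity: excluded by the second recording statement, included by the third. The text does not settle it.

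**Step 2: how much follow-up has recording free of attribution?** Inputs: a 7-day window per booster (Harms); two boosters in Group 1 and one in Group 2 (Intervention and comparator); follow-up to week 48, the last listed assessment, or 48 × 7 = 336 days.

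- Group 1: 2 × 7 = 14 days; 14/336 = 4.2% (14/365 = 3.8% if 12 months is taken as 365 days).
- Group 2: 7/336 = 2.1% (7/365 = 1.9%).
- Group 1, weeks 0 to 24 only: one window in 24 × 7 = 168 days; 7/168 = 4.2%.

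For about 96% of follow-up in Group 1 and 98% in Group 2, recording of a non-serious flare as an AE depends on attribution.

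**Step 3: what does the filter do to the comparison?** Let p be the true flare risk and a the probability that a flare is attributed to the vaccine, so the recorded risk is p × a. Then

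recorded ratio = (p_COVID / p_DT) × (a_COVID / a_DT).

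The ratio is distorted upwards if sites blame the COVID-19 booster more readily than the DT booster, and downwards if they blame it less readily. If attribution is equal, the ratio is kept but the difference shrinks by the factor a.

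Two illustrations follow. All risks and attribution rates in them are assumed; none comes from the documents.

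- True risk 20% in both arms, attribution 30% after COVID-19 and 5% after DT: 0.20 × 0.30 = 6% against 0.20 × 0.05 = 1%. The recorded ratio is 6 where the true ratio is 1.
- True risks 30% and 20%, attribution 10% in both arms: 0.30 × 0.10 = 3% against 0.20 × 0.10 = 2%. A true difference of 10 points is recorded as 1 point. With 280/2 = 140 per arm, the expected counts are 0.03 × 140 = 4.2 and 0.02 × 140 = 2.8, in place of 0.30 × 140 = 42 and 0.20 × 140 = 28.

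**The case against.** The strongest reply is that the article does not say flares are captured only through the general AE rule. Outcomes and Interim analyses both list flares separately from AEs. Infections and pregnancies are in the same safety list and are not governed by that rule either. Visit forms collect clinical data and concomitant medication, so a treatment change after a flare may leave a trace. The full protocol and the supplementary schedule are not shown and may contain a flare form. This stands as far as it goes: the absence of such a form from an article is no finding, and a reader who infers that flares are certain to go unrecorded goes further than the text allows. A form would not settle the matter, however. The outcome itself is defined as vaccine-induced, so the count would still depend on unblinded judgement.

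A second reply is that a flare judged not vaccine-induced lies outside the stated outcome and is not missing from it. That is literally so. But attribution in a single patient by staff who know the arm is a weak way to establish causation when a randomised contrast is available.

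Three stronger readings are tempting and are not supported:

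- That disease-related SAEs are not captured. The last recording statement in Harms can be read as covering every SAE.
- That the comparison has no denominator. The number randomised to each arm is known; only the numerator is filtered.
- That weeks 0 to 24 give the trial's only unbiased test of whether boosters cause flares. The COVID-19 versus DT contrast exists only in Group 1, it is not a comparison with no vaccine, and reporting would remain open-label even if every flare were recorded. Group 2 has its own randomised contrast of immediate with deferred vaccination.

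Excluding background disease events from an AE log is common and defensible where disease activity is not an outcome. Here it is one.

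**Conclusion.** The point holds for non-serious flares more than 7 days after a booster. The recording rule in Harms conflicts with the outcome list and the interim safety analysis, and the flare count rests on attribution by staff who know the arm. The comparison between arms can be biased in either direction. The extent in time is firm: about 96% of follow-up in Group 1 and 98% in Group 2. The size of any bias is unknown. The 6% versus 1% and 3% versus 2% figures show what assumed rates would do and are not estimates for this trial.

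For serious flares, the finding is only that two adjacent sentences disagree and must be reconciled. The conclusion assumes that the Harms text means what it says and that a flare counts as related to the qualifying condition. It concerns safety and DSMB oversight; the primary antibody endpoint is not affected. The change is worth making while participants are still being followed, because flares that were not recorded at the time may not be reliably recoverable later.

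**What to change.** Amend the Harms section so that flares or worsening of the qualifying condition are exempt from the exclusion. Record them as reported by the investigator, with date, severity and treatment change, in both arms from randomisation to week 48 whatever the attributed cause. State plainly that all SAEs are recorded, which removes the conflict between the two sentences.

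Redefine the safety outcome and the interim table as all flares by randomised arm, for the DSMB and for the final analysis. Use weeks 0 to 24 in Group 1 as the randomised COVID-19 versus DT booster contrast, with weeks 24 to 48 shown separately. Present Group 2 on its own. Keep vaccine attribution as a descriptive field.

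The cost is a protocol amendment, an eCRF form and more entries at visits where AEs are already reviewed. Table 1 spans many conditions, so investigator-reported worsening is more practical than a separate flare definition for each disease, at some loss of uniformity. Reporting would still be open-label: the change removes attribution as the condition for recording, but it does not remove differential reporting.

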### Participant timeline

The study design and participant timeline are shown in figure 1. Participants in Group 1 will have up to 11 visits over 12 months and those in Group 2 a maximum of 10.

**Figure 1 F1:**
[figure not shown]
Trial design. (a) Group 1: haemato-oncology and systemic autoimmunity disease participants. (b) Group 2: bone marrow transplant recipients. BMT, bone marrow transplant; DT, diphtheria/tetanus toxoids; Rand, randomisation; Scr, screening; Wk, study week.

### Sample size

The maximum sample size is 320 participants, 280 in the systemic autoimmunity and haemato-oncology group and 40 in the BMT recipient group. This sample size is based on previously calculated integrated time-weighted AUC of live anti-SARS-CoV-2 NAb titres following two SARS-CoV-2 vaccinations in healthy adults^25^ and patients infected with COVID-19.^26 27^ SD calculated from these datasets were 0.11 log_10_ and 0.12 log_10_, respectively. Assuming an SD of 0.12 log_10_, the study will have over 90% power to detect a 0.13 log_10_ difference in time weighted AUC log_10_ change from baseline (2-alpha=5%) within each sub-stratum of 40 participants. This corresponds to a 35% difference in live virus neutralisation titre between randomised arms. Time-weighted AUC allows for varying of follow-up of participants due to missed visits, loss to follow-up or death. We conservatively estimate overall lost to follow-up to be 10% and mortality 1% balanced across randomised sub-strata.

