### Randomisation

#### Sequence generation

Participants will be assigned to a study group based on their study-qualifying medical condition (table 1) using a central computer-generated randomisation sequence with a blocking factor of four created by the study statistician.

Participants in Group 1 will be stratified into one of two supra-stratum, haematological malignancy or systemic autoimmunity and then to sub-strata based on their planned treatment. Sub-strata include: haematological malignancy—chemotherapy; autoimmunity—B-cell depletion therapies; autoimmunity—anti-metabolite therapies; autoimmunity—TNFα-inhibition; autoimmunity—cyclophosphamide or alemtuzumab; autoimmunity—JAKi; autoimmunity—anti IL-17/23 monoclonal antibodies (table 1).

Group 1 participants will be randomised in a 1:1 ratio to receive either a COVID-19 booster at week 0 and a DT booster at week 24 (Arm A: immediate booster), or a DT booster at week 0 and a COVID-19 booster at week 24 (Arm B: deferred booster) (figure 1). Randomisation will be conducted using a central computer-generated random allocation algorithm using blocks and stratified by sub-strata population.

Group 2 has no sub-strata and participants will be randomised in a 1:1 ratio to receive either an immediate COVID-19 booster at week 0 (Arm C), or a deferred COVID-19 booster at week 24 (Arm D) (figure 1).

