### Statistical methods

#### Statistical methods for analysing primary and secondary outcomes

Baseline participant characteristics will be summarised by randomised arm for each sub-stratum separately and combined. Primary analyses will compare immunogenicity endpoints between randomised arms on an intention-to-treat basis, that is comparing participants as randomised regardless of whether they received immediate or deferred vaccinations according to the protocol. Log_10_ NAb titres will be summarised at each time point and presented graphically within each stratum. The primary outcome will be time-weighted AUC change from baseline in anti-SARS-CoV-2 log_10_ NAb titre over 12 months. The primary analysis will follow a modified intention to treat approach (mITT) and include all randomised participants with a baseline visit and at least one post baseline time point measured. This approach allows for the inclusion of all participants, even with partial follow-up. The AUC will be calculated for each participant using the trapezoidal rule based on all available data. To assess for bias due to missing data, a secondary analysis which will only include patients who completed the study and have no missing data will be performed. These results will be compared with the mITT analysis. Additionally, if the proportion of patients with missing data is over-represented in one study arm, additional sensitivity analyses will be performed. Randomised arms will be compared within each treatment stratum separately using simple, unadjusted two-sample t-tests. In the event of unbalanced baseline characteristics, adjusted comparisons using linear regression methods may be performed. Results will be presented as mean differences, 95% CIs and p values. There will be no adjustment of p values and CIs for multiple comparisons across the seven sub-strata. In addition to analyses within strata, analyses combining all strata will be performed. Analyses will test for different effects of immediate versus deferred vaccination in separate strata by testing for interactions between strata and randomised arm. These results will be presented as forest plots, by strata and overall. Analysis for Group 2 participants will be presented independently using similar approaches as above as appropriate.

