#### Methods to handle protocol non-adherence and methods to handle missing data

As indicated above, all participants with a minimum of two study visits will be included in the primary analysis, therefore including participants even with incomplete data at every time point, a strength of using an AUC endpoint. There will be no imputations for missing data in the primary outcome. Secondary analyses will also be conducted in a per-protocol (PP) population including only participants with available data at all time-points and received the scheduled interventions. Protocol non-adherers will also be excluded in the PP analyses.

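### Averaging each participant's AUC over whatever follow-up exists biases the primary contrast even when dropout is balanced and random, usually towards immediate boosting; the size rests on assumed kinetics and exit times

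*Protocol article*

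**What the plan says.** All references are to the protocol article.

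- **Estimator.** Under Statistical methods, the primary outcome is time-weighted AUC change from baseline in log10 neutralising antibody (NAb) titre over 12 months. "The AUC will be calculated for each participant using the trapezoidal rule based on all available data". The modified intention-to-treat set takes anyone randomised who has a baseline and one later value.
- **Missing data.** The section on non-adherence and missing data states: "There will be no imputations for missing data in the primary outcome". It calls the inclusion of incomplete records a strength of an AUC endpoint. The Sample size section makes the same claim: "Time-weighted AUC allows for varying of follow-up of participants due to missed visits, loss to follow-up or death". It expects 10% loss to follow-up and 1% mortality, balanced.
- **Booster timing.** Under Sequence generation, "Group 1 participants will be randomised in a 1:1 ratio to receive either a COVID-19 booster at week 0" (Arm A) or "a DT booster at week 0 and a COVID-19 booster at week 24 (Arm B: deferred booster"). Group 2 has the same week 0 against week 24 structure (Arms C and D).
- **Checks.** A completer analysis is set against the primary result, and a per-protocol analysis needs data at every time point. Both are unconditional and secondary. Further sensitivity analyses run only if missing data are concentrated in one arm.
- **Window.** The Outcomes section instead counts the 12 months from the booster.

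**The concern.** An average over observed time can stand in for the 12-month average only if the observed stretch is representative of the whole. Here it is not, and the two arms depart from it in opposite directions. Arm A rises early and then wanes, so a shortened record overstates its 12-month mean. Arm B has no COVID-19 booster until week 24, so a shortened record omits some or all of its response. The two errors add in the contrast.

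This needs neither informative nor unequal dropout. The plan's trigger for extra sensitivity analyses looks for imbalance between arms, so it is blind to this problem. At stake is the between-arm contrast that the trial exists to estimate, and the error usually runs in the direction of the hypothesis.

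**Working it through.** **1. The plan's own figure.** The Sample size section gives an SD of 0.12, a two-sided 5% level and 40 per sub-stratum, and claims: "the study will have over 90% power to detect a 0.13 log_10_ difference in time weighted AUC log_10_ change from baseline". With 20 per arm, SE = 0.12 × √(2/20) = 0.038 and 0.13/0.038 = 3.43. Power is 92.9% (normal) or 91.6% (noncentral t), so the stated figure reproduces. For pooled Group 1, with 140 per arm, SE = 0.12 × √(2/140) = 0.014.

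**2. Assumptions not in the documents.**
- The titre rises linearly over 4 weeks to a peak change P, then falls with a 90-day half-life: log10(2)/(90/7) = 0.0234 log10 per week, with the change floored at zero.
- Both arms have the same P. Arm B's change is zero until week 24.
- 12 months is 48 weeks, and the area is divided by observed time. The article does not spell out the divisor, but this is the ordinary meaning of time-weighted.
- Loss is 10% + 1% = 11% in each arm, unrelated to titre. All leavers have at least one post-baseline value.

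**3. Formula.** With A(T) and B(T) the mean change from baseline to exit week T:

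bias = 0.11 × {[A(T) − A(48)] − [B(T) − B(48)]}

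**4. Single exit times, P = 0.5.**
- Full follow-up: A peaks at week 4 and reaches zero 0.5/0.0234 = 21.4 weeks later. Its area is 0.5×4/2 + 0.5×21.4/2 = 6.34, and 6.34/48 = 0.132. B(48) is also 0.132, so the true difference is nil.
- Week 12: A = [1.0 + 8 × (0.500 + 0.313)/2]/12 = 0.354 and B = 0. Bias = 0.11 × (0.222 + 0.132) = 0.039.
- Week 24: A = [1.0 + 20 × (0.500 + 0.032)/2]/24 = 0.263 and B = 0. Bias = 0.11 × (0.131 + 0.132) = 0.029.
- Week 36: A = 0.176 and B = 0.118. Bias = 0.11 × (0.044 + 0.014) = 0.006.

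**5. Exits spread evenly** (A and B averaged over exit weeks, then the same formula).

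| P | A(48), B(48) | Weeks 4-48: mean A, B | Bias | Weeks 4-24: mean A (B = 0) | Bias |
|---|---|---|---|---|---|
| 0.3 | 0.053, 0.053 | 0.114, 0.026 | 0.010 | 0.163 | 0.018 |
| 0.5 | 0.132, 0.132 | 0.247, 0.053 | 0.021 | 0.323 | 0.036 |
| 1.0 | 0.487, 0.361 | 0.666, 0.122 | 0.046 | 0.734 | 0.067 |

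At P = 1.0 the arms already differ with full follow-up, because week 48 cuts off Arm B's response. The bias is added to that difference.

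**6. Scale.** For P = 0.5 and exits over weeks 4-48, the bias is 0.021/0.13 = 16% of the design difference. That is 0.021/0.038 ≈ 0.6 SE within a sub-stratum and 0.021/0.014 ≈ 1.5 SE in pooled Group 1.

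**7. Error rate.** A separate simulation used a 3-week rise, P = 0.6, a 12-week half-life, exits over weeks 4-48 and a true 48-week difference of zero. Bias was 0.027. The nominal 5% test rejected in 9.3% of runs at 20 per arm and about 40% at 140 per arm, nearly always in favour of Arm A. Across peaks of 0.3 to 1.0 and half-lives of 8 to 20 weeks, with Arm B's peak set so that the true difference was zero, the bias ran from 0.007 to 0.060. For exits over weeks 4-24 it ran from 0.014 to 0.088.

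**8. Waning in Arm B before its booster.** With exits over weeks 4-48 and waning of 0.01 or 0.02 log10 per week, the bias at P = 0.5 falls to 0.014 or 0.008. At P = 0.3 with 0.02 per week it reverses, to −0.004.

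**The case against.** - **The plan already has a check that works.** The completer comparison is unconditional and is aimed at bias from missing data. Under random dropout, which is what the calculation assumes, completers are unbiased (0.132 against 0.132 at P = 0.5), so the artefact would show. This stands. A reader might infer that nothing in the plan would detect the problem; the article does not support that. What remains is that the check is secondary, selects on completion if dropout is related to titre, and does not change the primary estimate.
- **The size can be made to look large.** A reader might take the week 12 and week 24 figures against the pooled SE and conclude that the bias is 2.0 to 2.7 SE. That puts every loss at one early date. It also uses the pooled comparison, whereas the plan powers and compares arms within sub-strata, where the same figures are 0.8 to 1.0 SE. The objection stands, so a range is the fair statement.
- **The direction is not guaranteed.** Waning in Arm B under new immunosuppression shrinks the bias and can reverse it for a weak response. This stands.
- **The window is unsettled.** If the 12 months run from the booster, Arm B leavers before week 24 have no post-booster window and their half of the mechanism changes. This stands as a condition. The baseline-anchored definition under Statistical methods and the 12-month visit span both favour the reading used here; 12 months after a week 24 booster would end at week 72. The other reading does not rescue the estimator, because the analysis set would still admit those leavers.

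**Conclusion.** The concern holds in qualified form. The mechanism follows from the article's own estimator and booster times: on a baseline-to-12-months window, balanced random dropout still biases the primary contrast, usually towards immediate boosting. The imbalance trigger would miss it, and the completer and per-protocol analyses would expose it only if dropout is unrelated to titre.

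The documents do not fix the size. On the stated assumptions it is about 0.01 to 0.046 log10 for exits over weeks 4-48 and about 0.02 to 0.07 for exits over weeks 4-24. This is modest within a sub-stratum and more serious in pooled Group 1.

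A reader might also infer that all dropouts contribute only a peak in Arm A and nothing from a booster in Arm B. That goes too far. It describes at most those who leave before week 24, and even their Arm A mean is 71% of the peak at week 12 (0.354/0.5) and 53% at week 24 (0.263/0.5). Exits at week 36 add only 0.006.

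**What to change.** 1. Reconcile the endpoint window in the Outcomes section (from the booster) with that under Statistical methods (from baseline).
2. Estimate the primary over one fixed week 0-48 window from a repeated-measures model of log10 NAb titre with baseline titre and arm-by-visit means. Fit it within each sub-stratum, or with arm × visit × sub-stratum terms, and also pooled. A pooled model with sub-stratum only as a covariate would not serve the planned within-stratum comparisons. Form the AUC contrast as the trapezoid-weighted sum of the visit means.
3. State in the estimand how deaths and Arm B participants who leave before week 24 are treated. Otherwise the model will implicitly project titres after death and a booster response in people who never received the booster.
4. Keep the per-participant AUC and the completer analysis as sensitivity analyses. Add a delta-adjusted analysis that runs whether or not missingness is balanced.

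The cost is protocol and analysis-plan wording and a little more programming, on data already being collected; the article places approval of the analysis plan before data lock. The downside is reliance on missing at random given observed titres, which is still weaker than the present implicit assumption that a shortened record represents the full 48 weeks.
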